## Methods and design

This is a single-blinded placebo-controlled RCT with three parallel groups (CSMT, placebo and control). Our primary hypothesis is that CSMT gives at least 25 % reduction in average number of headache days per month (30 days) as compared to no change in the placebo and the control group from baseline to the end of intervention, and we expect the same reduction to maintain at 3, 6 and 12 months follow-up. If the CSMT treatment is effective, it will be offered to participants whom received placebo or control after study completion, i.e., after 12 months follow-up. The study will adhere to the recommended clinical trial guidelines from the IHS (Tfelt-Hansen et al. 2000; Silberstein et al. 2008), and the methodological CONSORT guidelines (Moher et al. 2010).

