### Primary and secondary end-points

The primary and secondary end-points are listed in Table 2. The end-points adhere to the recommended IHS clinical trial guidelines (Tfelt-Hansen et al. 2000; Silberstein et al. 2008). We define number of headache days to be primary end-point and expect at least 25 % reduction in average number of days from baseline to the end of intervention, with the same level of reduction maintaining at follow-up. Based on previous reviews on CEH, a 25 % reduction is considered to be a conservative estimate (Chaibi and Russell 2012). A 25 % reduction from baseline to the end of intervention and follow-up is also expected in secondary end-points for headache duration, headache intensity, and headache index, where the index is calculated as mean days with headache (30 days) × mean headache duration (hours per day) × mean intensity (0–10 NRS). A 50 % reduction in medication consumption from baseline to the end of intervention and to follow-up is expected.

**Table 2 Tab2:** Primary and secondary end-points

Primary end-points
1. Number of headache days in active treatment vs. placebo group
2. Number of headache days in active treatment vs. control group
Secondary end-points
3. Headache duration in hours in active treatment vs. placebo group
4. Headache duration in hours in active treatment vs. control group
5. Self-reported VAS in active treatment vs. placebo group
6. Self-reported VAS in active treatment vs. control group
7. Headache index (frequency × duration × intensity) in active treatment vs. placebo group
8. Headache index in active treatment vs. control group
9. Headache medication dosage in active treatment vs. placebo group
10. Headache medication dosage in active treatment vs. control group

The data analysis is based on the run-in period vs. end of intervention. Point 11–40 will be duplicate of point 1–10 above at respectively 3, 6 and 12 months follow-up

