**Fig. 2 Fig2:**
[figure not shown]
Expected participants flow diagram

Change in primary and secondary end-points from baseline to the end of intervention and to follow-up will be compared between active and placebo and active and control group. Null-hypothesis states that there is no significant difference between the groups in average change, while the alternative hypothesis states that a difference of at least 25 % exists.

Due to follow-up period, repeated recordings of primary and secondary end-points will be available, and analyses of trend in primary and secondary end-points will be of main interest. Intra-individual correlations (cluster effect) are likely to be present in data with repeated measurements. Cluster effect will thus be assessed by an intra-class correlation coefficient (ICC) quantifying the proportion of total variation attributable to the intra-individual variations. The trend in end-points will be assessed by a linear regression model for longitudinal data (linear mixed model) to correctly account for possible cluster effect. Linear mixed model handles unbalanced data, enabling all available information from randomized patients to be included, also from drop-outs. Regression models with fixed effects for time component and group allocation as well as the interaction between the two will be estimated. The interaction will quantify possible differences between groups regarding time trend in the end-points and serve as an omnibus test. Random effects for patients will be included to adjust the estimates for intra-individual correlations. Random slopes will be considered. The linear mixed models will be estimated by SAS PROC MIXED procedure. The two pairwise comparisons will be performed by deriving individual time point contrasts within each group with the corresponding p values and 95 % confidence intervals (CI).

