### Power calculation

Sample size calculations are based on the results in a recently published group comparison study on topiramate (Silberstein et al. 2004). We hypothesize that the mean difference in reduction of number of days with headache per month between active and the placebo group is 2.5 days. The same difference is assumed between active and the control group. Standard deviation for reduction in each group is assumed to be equal 2.5. Under the assumption of on average 10 headache days per month at baseline in each group and no change in the placebo or control group during the study, 2.5 days reduction corresponds to a reduction by 25 %. As primary analysis includes two group-comparisons, we set a significance level at 0.025. A sample size of 20 patients is required in each group to detect a statistical significant mean difference in reduction of 25 % with 80 % power. To allow for drop-outs, the investigators plan to recruit at least 120 participants.

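### The sentence prescribing how the two primary comparisons are made uses contrasts within each group, which does not match the between-group question stated in the same section

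*Protocol article*

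**What the plan says.** All of this is in the protocol article.

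- **Question.** The text after Fig. 2 in Data processing says that change in the end-points will be compared between active and placebo and between active and control. It gives the null as "Null-hypothesis states that there is no significant difference between the groups in average change".
- **End-points.** The first primary end-point in Table 2 is "Number of headache days in active treatment vs. placebo group", and the second is the same against control. The note under the table bases the analysis on run-in against the end of intervention.
- **Time course.** Methods and design expects a reduction by the end of intervention and adds: "we expect the same reduction to maintain at 3, 6 and 12 months follow-up".
- **Power.** The Power calculation section starts from a between-group quantity: "We hypothesize that the mean difference in reduction of number of days with headache per month between active and the placebo group is 2.5 days". On alpha it says: "As primary analysis includes two group-comparisons, we set a significance level at 0.025".
- **Method.** A linear mixed model has fixed effects for time, group and their interaction. Of the interaction it says: "The interaction will quantify possible differences between groups regarding time trend in the end-points and serve as an omnibus test". Of the two primary comparisons it says: "The two pairwise comparisons will be performed by deriving individual time point contrasts within each group". The sentence ends by giving these contrasts their p values and 95 % confidence intervals.

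**The concern.** A time contrast within one group asks whether that arm differs from its own run-in value. Its p value and interval do not concern the difference between two arms, which is what the null, Table 2 and the sample size are about. The interaction does compare groups, but as an omnibus test it pools three arms and all time points. It is therefore neither CSMT against placebo nor CSMT against control at the end of intervention. As written, the 0.025 threshold is attached to no named between-group contrast at the primary time point.

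What is at stake is how the primary result could be read. Separate within-group p values invite the conclusion that CSMT worked because it changed significantly and sham did not. That reasoning credits CSMT with any change common to both arms, such as regression to the mean or a placebo response. The power calculation assumes no change in the comparators. However, the Discussion (Methodological considerations) describes the placebo response as high and possibly higher still in manual therapy.

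**Working it through.** **Step 1: reproduce the planned sample size.** The inputs, all from Power calculation, are a difference in reduction of 2.5 days, SD of the reduction 2.5 in each group, alpha 0.025 per comparison and power 80 %. Sidedness is not stated, so I take it as two-sided.

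n per arm = 2 × (z₀.₉₈₇₅ + z₀.₈₀)² × (SD/difference)² = 2 × (2.241 + 0.842)² × (2.5/2.5)² = 2 × 9.505 = 19.01, rounded up to 20.

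This matches the plan's 20 per group; a one-sided test would give 16. The figure is that of a two-sample comparison of change, so the trial was sized for a between-group test. At 20 per arm, power is 82.1 % by the normal approximation and 79.3 % by the exact t test.

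**Step 2: what the within-group contrasts would do if used to infer efficacy.** Suppose CSMT and sham have the same true mean reduction m, so that the true difference is zero. The SD of change is 2.5 (from the plan) and n is analysed per arm. The values of m are my assumption, shown as a range.

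- In each arm, test the change from run-in with a one-sample t test at two-sided 0.025. The probability of significance, P, comes from the noncentral t with n − 1 degrees of freedom and noncentrality (m/2.5) × √n.
- The arms are independent, so Pr(CSMT significant, sham not) = P × (1 − P).

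| True reduction in both arms (days) | P, n = 20 | P(1 − P), n = 20 | P, n = 40 | P(1 − P), n = 40 |
|---|---|---|---|---|
| 0 | 0.025 | 2.4 % | 0.025 | 2.4 % |
| 0.5 | 0.081 | 7.5 % | 0.155 | 13.1 % |
| 1.0 | 0.285 | 20.4 % | 0.582 | 24.3 % |
| 1.25 | 0.439 | 24.6 % | 0.793 | 16.4 % |
| 1.5 | 0.604 | 23.9 % | 0.924 | 7.1 % |
| 2.0 | 0.863 | 11.8 % | 0.996 | 0.4 % |

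For example, at m = 1.25 and n = 20 the noncentrality is 0.5 × √20 = 2.236, P = 0.439, and 0.439 × 0.561 = 0.246. P(1 − P) cannot exceed 0.25, so the figures near 25 % are the ceiling and not a typical value.

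**Step 3: the direct comparison.** The two-sample test of change errs in 2.5 % of trials (two-sided) whatever the common change m and whatever n.

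**Step 4: does recruiting 40 per arm remove the problem?** The target of 120 gives 40 per arm. At that size the rate is higher than at 20 for common changes of 0.5 and 1.0 day, and lower from 1.25 days upwards. A larger sample moves the peak but does not remove it.

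**The case against.** The strongest reply is that the intention is plain. The section states the between-group comparison and null before it reaches the model. The subject of the disputed sentence is the two pairwise comparisons, and elsewhere exactly two comparisons means CSMT against placebo and CSMT against control; purely within-group testing would give three arms at several times. One can read the sentence as deriving contrasts per group and then comparing them pairwise, and the planned model can supply that difference. This stands as a possible reading. It does not settle the matter, because the text never mentions the second step and gives the p values and intervals to the within-group contrasts.

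It is also fair that the inflation depends on the assumed common change. Under the plan's own assumption of no change in placebo or control, and no CSMT effect either, the rate is 2.4 %, so there is no inflation. That is why a range is shown.

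Three stronger readings go beyond the document:

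- A reader might infer that no between-group hypothesis is stated. It is, in the same section, in Table 2 and in the power calculation.
- A reader might infer that the sponsor has decided to judge efficacy on within-group significance. The null says otherwise; the wording only leaves that route open.
- A reader might infer from the emphasis on trend and the possible random slopes that time is fitted as a straight line, which would describe a drop-and-hold effect badly. The coding of time is not stated. 'Linear' describes the mixed model, random slopes are only to be considered, and contrasts at individual time points suggest discrete times.

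Finally, a separate analysis plan might name the right contrast. The point here is not an omission, however: the article does state a method for the primary comparisons, and that method disagrees with its own question.

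**Conclusion.** The point holds as a mismatch between the stated question and the stated method. The question, null, end-points and sample size are between groups, while the sentence that prescribes the two primary comparisons is within groups. Followed literally, it yields no test of either primary comparison at the end of intervention.

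The size of the consequence is conditional. It arises only if efficacy is inferred from CSMT being significant and sham not. It then ranges from no inflation when neither arm changes to roughly ten times the 2.5 % rate of the direct test at the worst common change (24.6 / 2.5 ≈ 10). These figures rest on the plan's SD of 2.5, equal true changes chosen for illustration, and two-sided tests. The placebo response that the Discussion anticipates makes a common change above zero plausible. Because the sentence governs the primary inference and is cheap to correct, it should be corrected before any comparative analysis.

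**What to change.** Replace the sentence on the pairwise comparisons with:

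> The two primary comparisons are the between-group contrasts (CSMT minus placebo, CSMT minus control) of change in headache days from run-in to the end of intervention, estimated from the group-by-time interaction with time as a categorical factor, each tested at 0.025. Within-group changes are descriptive, and the omnibus interaction is supportive.

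The cost is this wording plus ESTIMATE or LSMESTIMATE statements in the PROC MIXED model already planned. Categorical time uses a few more parameters. Alpha stays at 0.025 per comparison and the required sample size at 20 per arm; if all 40 per arm are analysed, power is 98.5 % (t test).

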Both per-protocol and intention-to-treat analyses will be conducted if relevant. All analyses will be performed by a statistician, blinded for group allocation and participants. All adverse effects will also be registered and presented. Participants who experience any sort of adverse effects during the trial period will be entitled to call the prime investigator on the project cell phone. The data will be analyzed with SPSS v22 and SAS v9.3. Because of two group-comparisons in a primary end-point, p values below 0.025 will be considered statistically significant. For all secondary end-points and analyses, a significance level of 0.05 will be used. Missing values might appear in incomplete interview questionnaires, incomplete headache diaries, missed intervention sessions and/or due to drop-outs. The pattern of missingness will be assessed and missing values handled adequately.

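### Holm's step-down test would keep the family-wise error at 0.05 and give the two primary comparisons more power than a fixed 0.025 for each

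*Protocol article*

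**What the plan says.** Table 2 lists two primary end-points. The first is "Number of headache days in active treatment vs. placebo group", and the second is the same count against the control group. The Data processing section gives the decision rule: "Because of two group-comparisons in a primary end-point, p values below 0.025 will be considered statistically significant". The abstract repeats it. The Power calculation section uses the same level: "As primary analysis includes two group-comparisons, we set a significance level at 0.025". Secondary end-points are not adjusted: "For all secondary end-points and analyses, a significance level of 0.05 will be used".

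No step-down or hierarchical rule appears. Each primary comparison must pass 0.025 whatever the other shows. The name Bonferroni is not used, but that is what the rule amounts to.

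The primary hypothesis in Methods and design sets a CSMT reduction of at least 25 % "as compared to no change in the placebo and the control group from baseline to the end of intervention", so both comparators matter to the stated objective. Estimates are to be reported with 95 % confidence intervals (abstract and Data processing).

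**The concern.** Once one of two null hypotheses has been rejected, only one can still be true, and it can be tested at the full 0.05 without breaching the family-wise limit. A fixed 0.025 for both leaves that allowance unused.

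The loss falls mainly on showing both comparisons. It also falls on whichever comparison has the smaller true effect. That could well be the sham comparison: the power calculation assumes no change under placebo, whereas the Discussion expects a high placebo response, possibly higher where attention and physical contact are involved. A trial that clearly beats usual care could then miss on sham with a p value between 0.025 and 0.05.

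**Working it through.** **Inputs.** From Power calculation: "the mean difference in reduction of number of days with headache per month between active and the placebo group is 2.5 days", with an equal value taken for CSMT against control; SD of the reduction 2.5 in all arms; level 0.025; power 80 %; 20 per group; at least 120 recruited. From Randomization: equal allocation, hence 40 per arm at recruitment and, through the shared CSMT arm, a correlation of 0.5 between the two test statistics. Sidedness is not stated. Two-sided is assumed because it reproduces the stated 20; one-sided 0.025 would give 16.

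**The article's own figure.** n = 2 × (SD/difference)² × (z₀.₉₈₇₅ + z₀.₈₀)² = 2 × 1 × (2.241 + 0.842)² = 19.01, rounded up to 20. The stated 20 per group reproduces. By noncentral t, power at 20 is 79.3 %.

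**Normal approximation at 20 per arm.** The standard error of a difference is 2.5 × √(2/20) = 0.791, so each statistic has mean 2.5/0.791 = 3.162. The critical values are 2.241 (for 0.025) and 1.960 (for 0.05).

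- Bonferroni, each: Φ(3.162 − 2.241) = 82.1 %.
- Bonferroni, both (bivariate normal, correlation 0.5): 71.7 %.
- Holm, both: P(first > 2.241, second > 1.960) + P(first > 1.960, second > 2.241) − P(both > 2.241) = 76.0 + 76.0 − 71.7 = 80.3 %.
- Holm, each: 82.1 + 76.0 − 71.7 = 86.5 % (from unrounded terms).
- At least one, under either rule: 82.1 + 82.1 − 71.7 = 92.6 % (from unrounded terms). Holm's first step is the same 0.025, so this cannot change.

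By this approximation, about 80 % power for both needs 24 per arm under Bonferroni and 20 under Holm.

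**Simulation with t tests** (variance pooled over three arms, 3n − 3 degrees of freedom, difference 2.5 for both comparisons):

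| Analysed per arm | Both: Bonferroni | Both: Holm | Each: Bonferroni | Each: Holm | At least one, either rule |
|---|---|---|---|---|---|
| 20 | 69.3 % | 78.7 % | 80.3 % | 85.0 % | 91.2 % |
| 30 | 90.0 % | 94.3 % | 94.3 % | 96.4 % | 98.5 % |
| 40 | 97.3 % | 98.7 % | 98.5 % | 99.2 % | 99.8 % |

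**Smaller difference against sham.** The assumption here, which is not a figure in the article, is that CSMT–placebo is 1.5 to 2.0 days and CSMT–control stays at 2.5. At 40 per arm, power against placebo rises from 66 % to 76 % (1.5 days) or from 90 % to 94 % (2.0 days). At 20 per arm and 1.5 days it rises from 35 % to 45 %.

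**Type I error.**

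- Both nulls true: any false rejection 4.6 % under either rule.
- CSMT equal to sham, 2.5 days better than control: the false claim over sham is 2.5 % under Bonferroni. Under Holm it is 4.3 % at 20 per arm and 4.9 % at 40.
- Same null with a very large effect against control: 2.5 % and 5.0 %.

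Neither rule exceeds 0.05.

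**The case against.** The strongest reply is that nothing here is wrong. The 0.025 rule is pre-specified, is stated alike in the abstract, Data processing and Power calculation, and fits the sample size. That stands: a reader might infer a type I error fault or an inconsistency, and the article shows neither.

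A second reply is that the gain of about 9 points belongs to 20 per arm, which is reached only if half of the 120 recruits are lost. The article gives no expected drop-out rate, and its mixed model keeps the available data from drop-outs. This also stands. With 40 per arm and the full 2.5-day effect, the joint gain is 1.4 points. Larger gains at 40 per arm need a smaller effect than the one planned.

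Third, Holm is not free. It nearly doubles the chance of a false claim over sham when CSMT beats only the unblinded control, and the Discussion itself raises attention bias for that group. It also lacks a simple matching interval, whereas 97.5 % intervals would match the present rule exactly. Both points stand as costs, although the error stays within 0.05.

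Fourth, a reader might take the primary hypothesis to mean that CSMT must beat both comparators for the trial to succeed, and conclude that it is underpowered at 69 %. The documents do not support that. Methods and design states an expectation against both groups, and Table 2 lists two separate primary end-points. If both wins were formally required, no split would be needed: each could be tested at 0.05, with joint power of just under 80 % at 20 per arm, slightly above Holm's.

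**Conclusion.** The point holds as a cheap gain in efficiency. Holm controls the same family-wise error with no added assumption, never loses a rejection the present rule would give, and leaves the calculated 20 per group intact. Under the article's assumptions, and two-sided testing, the gain in power for both comparisons is about 9 points at 20 analysed per arm, 4 at 30 and 1.4 at 40. Power for at least one success does not change. If the true difference from sham is 1.5 to 2.0 days, the sham comparison gains 4 to 10 points at 40 per arm. The improvement is worth making, but its absence does not invalidate the planned analysis.

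Whether the follow-up time points belong to the primary family is a separate question, which Holm on two tests does not settle.

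**What to change.** Replace the threshold sentence in Data processing, and its counterpart in the abstract, with: *The two primary comparisons are tested with the Holm procedure at family-wise 0.05: the smaller p value against 0.025 and, if significant, the other against 0.05.* Keep 0.025 in the power calculation, where it is conservative. Report 97.5 % intervals alongside the planned 95 % ones, and say that neither set corresponds exactly to the Holm decisions.

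The cost is one sentence and no new data or patients, plus the two downsides already named: no simple matching interval, and a higher false-positive rate on the sham comparison, still within 0.05.

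The change must be made and dated before the results are unblinded. Timing needs checking, because the article dates recruitment to September–October 2012, gives a trial duration of 16 months and cites a 2015 source. If the results have already been seen by group, the published 0.025 rule should stand.

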## Abstract

Cervicogenic headache (CEH) is a secondary headache which affects 1.0–4.6 % of the population. Although the costs are unknown, the health consequences are substantial for the individual; especially considering that they often suffers chronicity. Pharmacological management has no or only minor effect on CEH. Thus, we aim to assess the efficacy of chiropractic spinal manipulative therapy (CSMT) for CEH in a single-blinded placebo-controlled randomized clinical trial (RCT). According to the power calculations, we aim to recruit 120 participants to the RCT. Participants will be randomized into one of three groups; CSMT, placebo (sham manipulation) and control (usual non-manual management). The RCT consists of three stages: 1 month run-in, 3 months intervention and follow-up analyses at the end of intervention and 3, 6 and 12 months. Primary end-point is headache frequency, while headache duration, headache intensity, headache index (frequency × duration × intensity) and medicine consumption are secondary end-points. Primary analysis will assess a change in headache frequency from baseline to the end of intervention and to follow-up, where the groups CSMT and placebo and CSMT and control will be compared. Due to two group-comparisons, the results with p values below 0.025 will be considered statistically significant. For all secondary end-points and analyses, the significance level of 0.05 will be used. The results will be presented with the corresponding p values and 95 % confidence intervals. To our knowledge, this is the first prospective manual therapy three-armed single-blinded placebo-controlled RCT to be conducted for CEH. Current RCTs suggest efficacy in headache frequency, duration and intensity. However a firm conclusion requires clinical single-blinded placebo-controlled RCTs with few methodological shortcomings. The present study design adheres to the recommendations for pharmacological RCTs as far as possible and follows the recommended clinical trial guidelines by the International Headache Society.

*Trial registration* ClinicalTrials.gov identifier: NCT01687881, 2 December 2012

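### The two primary comparisons are tested at 0.025 but are to be shown with 95 % confidence intervals that are not labelled unadjusted, so test and interval can disagree

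*Protocol article*

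**What the plan says.** **Significance level.** The Data processing section, citing the two comparisons as the reason, states that for the primary end-point "p values below 0.025 will be considered statistically significant". The Abstract gives the same rule: "Due to two group-comparisons, the results with p values below 0.025 will be considered statistically significant". The Power calculation section uses 0.025 as well, for the same reason. For everything else, Data processing says: "For all secondary end-points and analyses, a significance level of 0.05 will be used".

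**Interval level.** Data processing describes how the two pairwise comparisons are obtained from the mixed model: by "deriving individual time point contrasts within each group with the corresponding p values and 95 % confidence intervals (CI"). The Abstract says of results in general: "The results will be presented with the corresponding p values and 95 % confidence intervals".

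Neither place makes an exception for the primary end-point, and neither says that the 95 % intervals are unadjusted for the two comparisons.

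**The concern.** A two-sided test at 0.025 corresponds to a 97.5 % interval, and a 95 % interval corresponds to a test at 0.05. For secondary end-points the article's two numbers agree (0.05 and 95 %). For the primary comparisons they do not.

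The consequence is a band of results, 0.025 ≤ p < 0.05, in which the published interval excludes zero while the plan calls the comparison non-significant. The article does not tell the reader how to take the interval in that case. What is at stake is how the primary result is reported and interpreted, and whether there is room afterwards to stress whichever of the two looks better.

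**Working it through.** **Inputs**
- Test level 0.025 per primary comparison (Abstract, Data processing, Power calculation); interval level 95 % (Abstract, Data processing).
- Difference 2.5 days, SD 2.5 in each group, 80 % power, 20 per group required, at least 120 recruited (Power calculation).
- Equal allocation to three arms (Randomization), so 120 / 3 = 40 per arm.
- The 20-per-arm case stands for heavy drop-out down to the required number, the 40-per-arm case for no loss.

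**1. The plan's own figure, and whether 0.025 is two-sided.** With a ratio of SD to difference of 1,

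n = 2 × (z₁₋α/₂ + z₀.₈₀)² = 2 × (2.241 + 0.842)² = 19.01, rounded up to 20.

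This matches the stated 20 per group. A one-sided 0.025 (equivalently a two-sided 0.05) gives 2 × (1.960 + 0.842)² = 15.7, so 16. The 0.025 is therefore two-sided and cannot be read as one tail of a 95 % interval.

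**2. The band of conflict.** The standard error of a difference is 2.5 × √(2/n). An observed difference conflicts when it lies between the two critical values:

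| Per arm | SE | 95 % half-width (t) | 97.5 % half-width (t) | Ratio |
|---|---|---|---|---|
| 20 (38 df) | 0.791 | 2.024 × 0.791 = 1.60 | 2.334 × 0.791 = 1.84 | 1.15 |
| 40 (78 df) | 0.559 | 1.991 × 0.559 = 1.11 | 2.285 × 0.559 = 1.28 | 1.15 |

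At 40 per arm, an observed difference between 1.11 and 1.28 days is thus non-significant under the plan although its 95 % interval excludes zero.

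**3. Chance of a conflict, per comparison.** This is the power at 0.05 minus the power at 0.025, from the noncentral t distribution:

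| True difference | 20 per arm | 40 per arm |
|---|---|---|
| 0 (null) | 2.5 % | 2.5 % |
| 1.25 days (assumption) | 33.8 − 23.8 = 10.0 % | 59.8 − 48.4 = 11.5 % (before rounding) |
| 1.5 days (assumption) | 45.6 − 34.2 = 11.4 % | 75.5 − 65.5 = 10.0 % |
| 2.5 days (planned) | 86.9 − 79.3 = 7.6 % | 99.3 − 98.5 = 0.8 % |

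The values of 1.25 and 1.5 days are not in the protocol. They are shown because the Power calculation assumes no change in the placebo and control groups, whereas Methodological considerations (Discussion) describes the placebo response as high and possibly higher still in manual therapy. A net difference from placebo below 2.5 days is therefore plausible on the article's own account.

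**4. Joint coverage.** Both contrasts use the CSMT arm. With equal n and equal SD their covariance is σ²/n and each variance is 2σ²/n, so the correlation is ρ = 0.5. For critical value c,

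P(both cover) = ∫ φ(u) × [Φ((c − √ρ·u)/√(1−ρ)) − Φ((−c − √ρ·u)/√(1−ρ))]² du.

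- c = 1.960 (95 %): 0.909.
- c = 2.241 (97.5 %): 0.954.

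Simulation with t quantiles gives 0.910 and 0.954 at both 20 and 40 per arm. Without any assumption on correlation, the Bonferroni lower bounds are 90 % and 95 %.

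**The case against.** The strongest reply is that the plan's decision rule is clear. Significance is defined by the p value alone, the sample size uses the same 0.025, and no sentence gives the interval a role in the decision. Unadjusted 95 % intervals beside an adjusted test are a common convention. Each has correct marginal coverage, and the article never claims simultaneous coverage, so 91 % contradicts no stated target. The general wording on 95 % intervals is also right for most of the results it covers, because secondary end-points are tested at 0.05. Finally, at 40 per arm and the planned effect a conflict is rare (0.8 %).

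All of that stands, and it limits the point. A reader might infer that the 95 % intervals undo the multiplicity control, or that they are wrong as intervals. The article supports neither reading: the control sits in the p-value rule, which is unchanged, and p values are to be shown beside the intervals.

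What the reply does not remove is the mismatch. The convention is sound when the intervals are labelled unadjusted, and here they are not. Nor is this a detail left to a fuller plan, since the article itself fixes both levels and they do not correspond for the primary comparisons.

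**Conclusion.** The point holds as a reporting inconsistency of low severity. For the two primary comparisons the stated interval level does not match the stated test level, so a result with 0.025 ≤ p < 0.05 would carry an interval that excludes zero while being non-significant under the plan. Type I error, power and sample size are unaffected.

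Its practical size depends on the true effect and on retention: under 1 % per comparison if the planned effect holds with no loss from 40 per arm, and roughly one comparison in nine or ten if the net effect is about half to 60 % of the planned one. These chances assume SD 2.5 and a simple two-group t comparison of changes; the planned mixed model may shift them somewhat. The 91 % joint coverage further assumes equal allocation and equal SD.

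**What to change.** In the Abstract and in Data processing, state that the two primary comparisons are presented with 97.5 % confidence intervals and all other results with 95 % confidence intervals. If 95 % intervals are also kept for the primary comparisons, label them as unadjusted and not used to judge significance.

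The cost is one sentence in each place and a changed confidence level for the primary contrasts in the software. No further patients are needed. The downside is that the primary intervals become about 15 % wider: at 40 per arm and SD 2.5, a half-width of 1.28 days instead of 1.11.
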